### Saliva

Saliva samples will be collected by spitting into a prelabelled sterile 5mL screw cap collection tube, (6101S, Growing Labs, Suwanee, GA) before cleaning teeth or eating in the morning. After collecting 1.5ml of liquid saliva, 1.5mL of RPB will be added, the sample shaken vigorously for 15 seconds, then stored in a zip-lock bag and frozen at -20°C until transfer to -80°C freezer.

### Environmental samples

To determine interactions with mould exposure in the home (and/or workplace), participants will be asked to take surface swabs from six unique sites in their indoor environment where mould is visible, or typically grows. A list of likely places will be provided. After collecting a sample with a sterile flocked swab (Hydraflock, 25-3206-H, Puritan Medical Products, Guildford, ME), the swab tip is snapped into a pre-labelled tube containing RPB. The site of sample collection is matched to the tube identifier on a logging sheet, including a description of the sample and site collected from.

### Metatranscriptomic analysis: blood, stool, saliva & environmental samples

Samples will be analysed by Viome Life Sciences using metatranscriptomics, developed for analysis of human clinical samples. The method has been described for faecal samples [29], saliva [30], and blood [31]. In this study, it will also be applied to environmental samples. After mixing with preservative (as detailed for each sample), the RNA is stable for up to 4 weeks at ambient temperature.

Prior to analysis, samples are lysed using a combination of mechanical (bead beating) and chemical lysis (detergents and denaturants). Most downstream methods are automated and performed by Hamilton Star liquid handlers. Total nucleic acids are purified from clarified lysates using a bead-based method. DNA is degraded enzymatically, and heat inactivated. Removal of non-informative RNAs (RNR) is done with a subtractive hybridisation method. Currently, 132 microbial probes that target microbial rRNAs and 80 human probes that target abundant human transcripts (rRNA, globin, etc.,) are utilised. Microbial probes are applied to stool and surface swab samples, human probes are applied to blood samples, and a combination of microbial and human probes are applied to saliva samples. After RNR, the remaining RNAs are converted into cDNA, then size-selected for Illumina sequencers using the spri bead technology. Final libraries are created with limited cycles of PCR that also adds unique dual barcodes to each sample. Libraries from individual samples are pooled and purified/size selected using either spri beads or Pippin prep (​​Sage Science). Library pools are sequenced on an Illumina NavSeq 6000 instrument using 2x150 sequencing chemistry. Bcl files are demultiplexed using bcl2fastq software and fastq files are processed using Viome Life Sciences proprietary, cloud-based software. The bioinformatic output from each sample type includes genome- and species-level taxonomic classification (including relative abundance), relative abundance of microbial Kyoto Encyclopaedia of Genes and Genomes (KEGG) orthologs, and quantitative expression of human genes.

Dried blood spot samples will be analysed using the Viome Multiplexed Immunoassay (VMI). This is a combination of serology and ELISA tests, using optically encoded Luminex beads for performing multiple analyses in one reaction. Currently, VMI comprises serology tests that quantify immunoglobulin (IgG) antibodies against 46 foods and human thyroid peroxidase, high sensitivity C-reactive protein (ELISA), and tumour necrosis factor-α (ELISA).

The VMI method starts with elution of whole blood from the dried blood spot (Whatman®) cards. The elution is incubated with beads for one hour, then the beads are washed. For serology tests, a detection antibody conjugated to phycoerythrin is added. For ELISA tests, the secondary antibody is added, followed by the detection antibody, also conjugated to phycoerythrin. Beads are counted and imaged using the MAGPIX system (Luminex) to obtain the median fluorescence intensity (MFI) for each test. Using calibration (standard) curves, the MFI values are converted to analyte concentrations.

### Urine samples

Intestinal hyperpermeability is a phenomenon in which leakage of molecules and ions below ~0.4nm [32] occurs through what are normally tight epithelial cell junctions in the gut lumen [33]. Increased paracellular leakage has been implicated in many disorders, including fibromyalgia [34].

At the initial appointment, a pack is provided with collection equipment, 3x 10mL Fisherbrand™ transport tube (Fisher Scientific 13-711-20, Globe Scientific, Mahwah, NJ) labelled #1, #2 & #3, and with identifier code. Detailed instructions, including a link to a video on YouTube and a checklist/log sheet is provided for recording of times and urine volumes.

The test involves a 4-hour urine collection, completed at home, with urine aliquots at baseline, and 2 and 4-hours after ingestion of a lactulose and mannitol challenge drink, as detailed by Sequiera et al [35]. Participants are instructed to avoid collecting while menstruating, abstain from non-steroidal anti-inflammatory drugs for at least two days, abstain from alcohol, aspirin, probiotics, and mannitol-containing foods (cauliflower, mushrooms, strawberries, onions, pumpkin, sweets, chewing gums or substances with artificial sweeteners) the day before testing and adhere to the collection protocol as outlined.

Other than water as detailed, no food or fluid is permitted until completion of sample collection. Participants will also be asked to note any symptoms occurring during the test and during the following 6 hours.

In a fasting state, from the first morning urination, a ~9mL sample is transferred into tube #1 and frozen as soon as possible.

The test substrates – 15mL lactulose BP 3.34g/5mL (Laevolac, Douglas Pharmaceuticals, NZ) and 5g d-mannitol AR (31501, ECP Labchem Ltd, NZ), dissolved in 250mL water - are then ingested. For the following 4 hours all urine passed is collected and transferred into a graduated 1L container (JC1000N, SprayPac, NZ) pre-spotted with 1mL chlorhexidine gluconate 20% (RN Laboratories, India; Amtrade NZ, FP/I/20/0895).

Two hours after taking the test solution, participants urinate and add all the urine passed to the 1L container provided, note the total volume, then extract 9mL, using a disposable graduated transfer pipette (Fisherbrand™, 13-711-20, Fisher Scientific, Waltham, MA). At this point they will drink 250mL of water and continue to collect all urine passed for a further two hours.

Four hours after ingesting the test substrate, participants will empty their bladder, adding all urine passed to the 1L container. After recording the total volume of urine now in the 1L container, a final 9mL sample will be pipetted off into the third tube. All samples will be stored frozen until returning them to the study site, where they are either centrifuged immediately or transferred to a -20°C freezer.

Thawed samples will be spun at 2075 relative centrifugal force for 5 minutes to remove debris and cellular particles. From each 9mL tube, urine will then be aliquoted into 2x 2mL microtubes (Scientific Specialties Inc., 3621-875, Interlab, Wellington, NZ) and baseline samples spotted with 2μL of 20% chlorhexidine. Labelled tubes are then transferred into cardboard freezer boxes before returning to the freezer.

For the analysis, recoveries of lactulose and mannitol will be determined using high performance liquid chromatography, after calibrating with specified concentrations of each. The full calibration procedure is outlined elsewhere [36]. The quantity of sugars in each urine sample is determined by multiplication of the relevant concentration (mg/mL) and the volume of accumulated urine at that time point. The result is expressed as a percentage of the original dose ingested.

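### The sugar recovery formula has no baseline term, so any mannitol already in the urine before dosing counts as recovered test dose

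*Protocol article*

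**What the plan says.** The Urine samples section describes three tubes. For the first, before the drink: "In a fasting state, from the first morning urination, a ~9mL sample is transferred into tube #1 and frozen as soon as possible". The participant then takes "15mL lactulose BP 3.34g/5mL (Laevolac, Douglas Pharmaceuticals, NZ) and 5g d-mannitol AR" in water and collects all urine for 4 hours in one container. At 2 hours the accumulated volume is noted and 9 mL is removed. At 4 hours: "After recording the total volume of urine now in the 1L container, a final 9mL sample will be pipetted off into the third tube".

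The calculation is written out: the "quantity of sugars in each urine sample is determined by multiplication of the relevant concentration (mg/mL) and the volume of accumulated urine" at the time point concerned. It continues: "The result is expressed as a percentage of the original dose ingested".

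The volume of the first-morning void and the time of the previous void are not specifically requested, although "a checklist/log sheet is provided for recording of times and urine volumes". The baseline tube is aliquoted and preserved with the others, but the text states neither its purpose nor its place in the calculation.

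**The concern.** A recovery test should count only sugar that came from the test dose. The stated formula counts all sugar measured at 2 and 4 hours. For mannitol these can differ, because mannitol also comes from food. The protocol recognises this by asking participants to avoid mannitol-containing foods and artificial sweeteners, but only on the day before and without supervision. A pre-dose sample that could show the remaining background is in hand, yet the formula does not use it.

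Applied to the baseline tube itself, the formula has no clear meaning: collection has not begun and no dose has been taken.

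At stake is the accuracy of percentage mannitol recovery. The error would vary from woman to woman with her recent diet, so it would add noise. It would also add bias to the case-control comparison if background differed between the groups.

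**Working it through.** The plan states no recovery figure, so there is none to reproduce. The check is direct arithmetic.

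**Inputs from the protocol.** Mannitol dose 5 g = 5000 mg. Lactulose dose 15 mL × 3.34 g / 5 mL = 10.02 g. Volumes V2 and V4 are recorded at 2 and 4 hours; 9 mL is removed at 2 hours.

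**Assumed inputs (the documents give none).** Background mannitol in the pooled 4-hour urine 0.02 to 0.2 mg/mL; V4 = 500 mL; true mannitol recovery 10% or 15%.

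**1. Size of the uncorrected background.** As written, R = 100 × C4 × V4 / dose.

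- Background amount: 0.02 × 500 = 10 mg to 0.2 × 500 = 100 mg.
- In percentage points of dose: 10/5000 = 0.2 to 100/5000 = 2.0.
- Relative error at 15% recovery (750 mg): 10/750 = 1.3% to 100/750 = 13.3%.
- Relative error at 10% recovery (500 mg): 10/500 = 2% to 100/500 = 20%.
- If background is zero, the error is zero.

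**2. Two possible corrections.** Let C0 be the tube #1 concentration, V0 the first-void volume and T0 the hours since the previous void.

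- By concentration: R = 100 × (C4 − C0) × V4 / dose. No baseline volume is needed.
- By excretion rate: R = 100 × (C4 × V4 − 4 × C0 × V0 / T0) / dose. V0 and T0 are needed.

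Illustration with assumed C4 = 2 mg/mL, V4 = 500 mL, C0 = 0.05 mg/mL:

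- As written: 100 × 2 × 500 / 5000 = 20.0%.
- By concentration: 100 × 1.95 × 500 / 5000 = 19.5%, a reduction of 0.50 points.
- By rate, V0 = 200 mL, T0 = 8 h: 4 × 0.05 × 200 / 8 = 5 mg, a reduction of 0.10 points.
- By rate, V0 = 500 mL, T0 = 6 h: 4 × 0.05 × 500 / 6 = 16.7 mg, a reduction of 0.33 points.

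The concentration method therefore removes 1.5 to 5 times as much as the rate method (0.50/0.33 to 0.50/0.10). Overnight urine is likely to be more concentrated than urine passed after the 250 mL drink and the further 250 mL of water at 2 hours, so subtracting C0 directly may remove too much. The choice affects the answer and should not be made after seeing the data.

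**3. An error in the other direction.** The 9 mL removed at 2 hours is no longer in the container when the 4-hour volume is read. The sugar lost is 9 × C2, which is a share 9/V2 of the 0–2 hour amount: 18% at V2 = 50 mL, 9% at 100 mL, 4.5% at 200 mL and 2.25% at 400 mL. For mannitol at an assumed C2 of 1 to 5 mg/mL, this is 9/5000 = 0.18 to 45/5000 = 0.9 percentage points, lowering 4-hour recovery.

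**The case against.** The strongest reply is that this is a condensed article. It refers to cited sources for the collection procedure and the calibration, so a baseline correction may be specified there, and the log sheet may already capture the first void. The restriction on mannitol foods, the fasting state and the ban on food during collection all reduce background. Permeability is not named under Objectives or in the conceptual framework, so little depends on it.

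Much of this stands, and it limits the point to a minor one. It does not remove it, because the article states the recovery formula itself, and that formula has no baseline term.

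A reader might infer more than the documents support:

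- **That no correction can be derived without a baseline volume.** This is wrong. The concentration method needs only tube #1 and the recorded 2- and 4-hour volumes.
- **That recovery is overstated as a matter of fact.** This needs a non-zero background, for which no figure is given, and the 9 mL withdrawal pulls 4-hour recovery down.
- **That lactulose is affected too.** The Lactulose breath test section describes it as synthetic, so pre-dose lactulose should be about zero. No minimum interval is stated between the urine and breath tests, but nothing shows them close enough for carry-over.
- **That a lactulose-to-mannitol ratio is biased and leakiness understated.** The protocol names no such ratio; it reports recovery as a percentage of dose.
- **That tube #1 was collected for this correction.** That is a natural guess, but its purpose is not stated.

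**Conclusion.** The point holds in a limited form, for mannitol. The stated formula takes no account of sugar present before dosing, so mannitol recovery may be overstated whenever baseline mannitol is not zero. The relative error of about 1% to 13%, or 2% to 20% at the lower recovery, rests wholly on the assumed background, urine volume and true recovery, and scales directly with the background. The net direction of error at 4 hours cannot be settled from the documents, because the missing baseline term and the uncounted 9 mL act in opposite directions. A difference in bias between cases and controls is possible but not shown, since both groups follow the same pre-test instructions. Severity is minor: a secondary measure with an inexpensive remedy.

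**What to change.** State before analysis how the baseline tube enters the calculation.

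- Add two entries to the existing log sheet: total volume of the first-morning void and time of the previous void.
- Compute the baseline excretion rate r = C0 × V0 / T0 for mannitol.
- At 2 hours: recovery = 100 × (C2 × V2 − 2r) / dose.
- At 4 hours: recovery = 100 × (C4 × V4 + 9 × C2 − 4r) / dose. The middle term restores the sugar in the 9 mL withdrawn; apply it to lactulose as well.
- Where the first-void volume was not recorded, use concentration subtraction, or flag tests whose baseline concentration exceeds a limit set in advance relative to the 2-hour sample.
- Report uncorrected recovery as a sensitivity analysis.

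The cost is two entries on a form already in use and a revised formula; tube #1 is already collected and stored. There are two downsides. Self-reported void times add some noise. Carrying a constant overnight rate forward may over-correct if dietary mannitol is still clearing, which is one reason to show the uncorrected result alongside.

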#### Redox status

Finally, two separate blood samples (20µl and 50µl) will be collected from a capillary finger prick for evaluation of free oxygen radicals (FORT) and free oxygen radical defenses (FORD) according to the manufacturer’s instructions [27].

The FORT/FORD test is a reliable measure of whole blood oxidative stress [28]. It is a colorimetric assay, using disposables purchased as commercially available kits (BioMed Science/ Callegari Sr, Italy). The filled capillary tubes are immediately added to a 2mL tube with supplied reagents, centrifuged (CR6000), and analysed in the automated dedicated spectrophotometer (CR3000 RCH, FormPlus, Callegari, Parma, Italy).

FORT is an indirect measure of reactive by-products in whole blood. It is based on Fenton’s reaction, determining the capacity of transition metal ions (Fe^3+^ /Fe^2+^) to catalyse the breakdown of hydroperoxides (R-OOH) into derivative radicals [alkoxyl (R-O•) and peroxyl radicals (R-OO•)]. FORT units are expressed as equivalent concentrations of H_2_O_2_ mmol/L^-^1, with one FORT unit corresponding to approximately 7.6 mmol/L of H_2_O_2_ (equivalent to 0.26 mg/L) [27].

FORD is an indirect measure of the antioxidant capacity in whole blood. It is based on the capacity of ascorbic acid, glutathione, and albumin in the sample to reduce a preformed radical cation. FORD is expressed as mmol/l of Trolox (6-hydroxy-2,5,7,8-tetramethylchroman-2-carboxylic acid; a water-soluble analogue of vitamin E) [27].

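### The 4-hour urinary sugar recovery omits the 9 mL removed at 2 hours, and the two figures given for one FORT unit disagree by a factor of about 1,000

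*Protocol article*

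**What the plan says.** **Urine (protocol article, Urine samples).** After the lactulose-mannitol drink, all urine goes into one 1 L container. At 2 hours participants add what they pass and "note the total volume, then extract 9mL, using a disposable graduated transfer pipette". Collection into the same container then continues for two more hours. The last sample is drawn at 4 hours: "After recording the total volume of urine now in the 1L container", a further 9 mL goes into the third tube. The quantity of each sugar is its concentration multiplied by "the volume of accumulated urine at that time point", reported as a percentage of the dose. No step returns the contents of the 2-hour aliquot to the 4-hour total.

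**FORT (protocol article, Redox status).** The article says "FORT units are expressed as equivalent concentrations of H_2_O_2_ mmol/L" and gives the conversion as "one FORT unit corresponding to approximately 7.6 mmol/L of H_2_O_2_ (equivalent to 0.26 mg/L".

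**The concern.** In a cumulative collection, anything taken out of the container part-way must be added back at the concentration it had when removed. The article fixes both the collection steps and the formula, and together they do not do this. The 4-hour recovery is then too low, and by an amount that depends on how much urine the woman had passed by 2 hours. The error is therefore not a constant that cancels between participants.

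For FORT, a molar and a mass concentration of the same substance are called equivalent, and they can be checked against its molar mass. If the molar figure is the wrong one, values converted with it would be about 1,000 times too high and could not be set beside other published data.

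**Working it through.** **Urine: inputs.** From the article: 9 mL removed at 2 hours, with the volume V2 noted before removal; the same container used to 4 hours; V4 recorded as the content at 4 hours, before the last aliquot is drawn. Not in the article, so assumed: V2 of 100 to 300 mL, and a share f of 30% to 70% of the 4-hour excretion falling in 0-2 h.

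**Urine: mass balance.** Let C2 and C4 be the concentrations in the 2-hour and 4-hour samples.

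- At 2 hours: amount = C2 x V2. This is complete, because V2 is noted before the 9 mL is taken.
- At 4 hours: V4 = V2 - 9 + (urine passed from 2 to 4 h).
- Rule as written: C4 x V4.
- Full excretion: C4 x V4 + C2 x 9.
- Omitted: C2 x 9, which is 9/V2 of the 0-2 h amount, or f x 9/V2 of the 4-hour total.

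Relative shortfall in the 4-hour recovery, f x 9/V2:

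| V2 | 9/V2 | f = 30% | f = 50% | f = 70% |
|---|---|---|---|---|
| 100 mL | 9.0% | 2.7% | 4.5% | 6.3% |
| 150 mL | 6.0% | 1.8% | 3.0% | 4.2% |
| 200 mL | 4.5% | 1.35% | 2.25% | 3.15% |
| 300 mL | 3.0% | 0.9% | 1.5% | 2.1% |

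Outside that volume range, with the same f, the shortfall is 5.4% to 12.6% at V2 = 50 mL and about 0.5% to 1.3% at 500 mL. The dose is a fixed denominator, so the same relative error carries to the percentage of dose.

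**Urine: worked case.** Take 100 units excreted in 4 hours, f = 50%, V2 = 100 mL and 150 mL passed from 2 to 4 h.

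- C2 = 50/100 = 0.5 per mL, so the aliquot removes 9 x 0.5 = 4.5 units.
- V4 = 100 - 9 + 150 = 241 mL and C4 = 95.5/241 = 0.396 per mL.
- Rule as written: C4 x V4 = 95.5.
- With the aliquot added back: 95.5 + 4.5 = 100.

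**FORT.** The molar mass of hydrogen peroxide is 2 x 1.008 + 2 x 15.999 = 34.01 g/mol.

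- 7.6 mmol/L x 34.01 mg/mmol = 258.5 mg/L. The stated 0.26 mg/L is not reproduced.
- 0.26 mg/L / 34.01 mg/mmol = 0.0076 mmol/L = 7.6 micromol/L.
- 7.6 micromol/L = 0.0076 mmol/L, and 0.0076 x 34.01 = 0.2585 mg/L, which rounds to the stated 0.26.
- Ratio of the stated molar figure to the one implied by the mass figure: 7.6/0.00764 = 994, that is 1,000 after rounding.

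**The case against.** **The word accumulated could cover all urine passed, including the 9 mL.** The rule would then be C4 x (V4 + 9). This narrows the error but does not remove it, because the aliquot is counted at C4 instead of C2, leaving 9 x (C4 - C2). In the worked case it gives 0.396 x 250 = 99.1. Over V2 of 50 to 500 mL, with 150 to 300 mL passed from 2 to 4 h, the result ran from about 10% low to about 1% high, and stayed within about 4% once V2 was 100 mL or more. On this reading the problem is smaller, but the formula is still not right.

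**The detail may lie in the method papers that the article cites.** They may contain the correction, and this cannot be seen. The article nevertheless writes out its own steps and formula, and as written these omit the aliquot.

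**The effect is small.** This stands. Only the 4-hour figure is affected, the size rests on assumed volumes and shares, and no effect on the case-control comparison has been shown. A reader might infer a biased lactulose/mannitol ratio. The article names no such ratio, and much of the loss would cancel in one: with assumed 0-2 h shares of 60% for mannitol and 40% for lactulose, it would be about 1.9% high at V2 = 100 mL and 0.6% high at 300 mL.

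**The FORT figures may be a slip in a unit prefix.** That is plausible. Readings come from a dedicated automated analyser, and a constant factor leaves t-tests, correlations and rank methods unchanged.

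**A reader might also infer that the missing use of the baseline urine (tube #1) is an error.** The article does not support that. It is silent on how tube #1 enters the calculation, which a condensed article may leave to the full method. Nor is subtraction an obvious remedy: a concentration cannot be taken from an amount, and first-morning fasting urine may be more concentrated than samples passed after 250 mL and then another 250 mL of fluid.

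**Conclusion.** Both points hold in limited form. Read literally, the 4-hour lactulose and mannitol recoveries leave out C2 x 9 mL and are about 0.9% to 6.3% low in relative terms, given V2 of 100 to 300 mL and 30% to 70% of excretion in the first 2 hours. The omission itself follows from the text; its size depends on those two assumptions. The 2-hour recovery is right.

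The FORT contradiction needs no assumption: the two figures cannot both be correct. The mass figure "equivalent to 0.26 mg/L" agrees with 7.6 micromol/L, which points to the molar unit. A reader might conclude that reported FORT values will be 1,000 times too high, but the article alone does not prove which figure is misprinted, or that this conversion will be applied to the analyser output. The consequence is confined to absolute values in mmol/L and comparison with other studies.

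Neither point undermines the primary aim, which concerns the microbiota, digestive symptoms and clinical presentation. Redox balance is listed under Objectives as an additional evaluation.

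**What to change.** **Urine.** State the 4-hour amount as C4 x recorded 4-hour volume + C2 x 9 mL, then divide by the dose. Leave the 2-hour formula as it is. Both concentrations come from tubes #2 and #3, and the volumes are already on the participant's log sheet. The cost is one line in the calculation, which can also be applied to data already collected.

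**FORT.** Check the unit of the conversion against the manufacturer's documentation, make the molar and mass figures agree, and report nothing in mmol/L until that is done. The cost is one check and a one-line correction. No samples, visits or procedures change for either point.
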